## Objectives

The principal objective aims to determine, 6 months after inclusion, whether the OptiMA strategy or ComPAS strategy leads to a favourable outcome which is non-inferior to what Niger standard protocol, in use in the same outpatient health facilities, provides. The definition of a favourable outcome is described in the “Study outcomes” section.

Two main secondary objectives for this trial are as follows. The first one is to determine whether the recovery rate of children with uncomplicated SAM according to the current WHO definition [14] (e.g. MUAC < 115 mm or WHZ < − 3 or bilateral oedema) managed under the simplified OptiMA or ComPAS strategies is non-inferior to that of the national standard protocol of Niger. The second one is to determine whether the recovery rate of children admitted with MUAC < 115 mm or oedema (+, ++) managed under the simplified OptiMA or ComPAS strategies is non-inferior to that of the national standard protocol of Niger.

Other secondary objectives include description and comparison between the three study arms of the following outcomes: cost-effectiveness analysis, RUTF consumption, relapse after nutritional recovery, non-response after outpatient follow-up, recovery, and success in children who present with both wasting and stunting at inclusion, and to describe the nutritional and clinical status of children hospitalised while enrolled in the study.

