### Study outcomes

The primary outcome will be judged by a binary composite indicator. Children classified as “favourable outcome” fulfil all of the following criteria: alive, not acutely malnourished per the anthropometric definition applied at inclusion (MUAC > 125mm and WHZ > − 3, and no oedema) and not having an additional episode of AM throughout the 6-month observation period. This outcome is measured at 6 months after randomisation. All other children are classified as “unfavourable outcome”.

The main secondary outcome #1 will be determined among children who meet the current WHO definition of SAM at inclusion (MUAC < 115 mm or WHZ < − 3 or oedema +, ++). The main secondary outcome #2 will be determined among children admitted with a MUAC < 115mm or oedema (+, ++). For these two subgroups, recovery is defined in each arm by a 4-week minimum duration of treatment, an axillary temperature < 37.5 °C, and an absence of bipedal oedema and a MUAC ≥ 125 mm for two consecutive weeks. This outcome is measured throughout the 6 months post-randomisation, meaning a child will be considered as recovered if he reaches these criteria during the 6-month follow-up in outpatient or village visits. Additional secondary outcomes are listed in Table 1.

**Table 1 Tab1:** Primary and secondary outcomes in the OptiMA Niger trial

	Measurement variable	Method of aggregation	Time point

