**Main secondary**			
Recovery	Composite: absence of bipedal oedema and a MUAC > 125 mm for two consecutive weeks, a 4-week minimum duration of RUTF treatment, and a good clinical health (without fever)	Proportion	Throughout the 6-month follow-up period
**Secondary**^a^			
Cost-effectiveness	Incremental cost-effectiveness ratio (ICER)	Ratio	Throughout the 6-month follow-up period
Consumption of RUTF per children with a favourable outcome	Sachets of RUTF consumed	Mean	6-month post-inclusion
Consumption of RUTF per recovered children	Sachets of RUTF consumed	Mean	End of RUTF treatment initiated at inclusion
Average daily weight gain in SAM children recovered	g/kg/day	Daily	End of RUTF treatment initiated at inclusion
Average daily MUAC gain in SAM children recovered	mm/day	Daily	End of RUTF treatment initiated at inclusion
Hospitalisation	Children with at least one episode of hospitalisation	Proportion	Throughout the 6-month follow-up period
Relapse to a new episode	Children with MUAC < 125 or WHZ < − 3 *Z*-score or oedema after RUTF treatment	Proportion	After recovering from the first episode of acute malnutrition
Non-response	Children who did not reach the recovery criteria	Proportion	16 weeks after inclusion
WaST	Children associated with severe and moderate stunting with acute malnutrition	Proportion	Throughout the 6-month follow-up period

^a^All the secondary outcomes will be analysed for the overall population (MUAC < 125 mm or WHZ < − 3 or oedema) and for the secondary populations (SAM WHO and MUAC < 115 mm or oedema)

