### Intervention

Table 2 summarises the difference in treatment eligibility, recovery definition, and exit criteria between the current national protocol in Niger, OptiMA, and ComPAS strategies. The RUTF ration per week according to standard, OptiMA, and ComPAS strategies are detailed in Additional file 3.

**Table 2 Tab2:** Wasting definition, treatment products, calculation of dosage, and recovery definition in the Niger national, OptiMA, and ComPAS protocols

	National Niger protocol			OptiMA protocol			ComPAS protocol	
	SAM	MAM		Acute malnutrition			Acute malnutrition	
*Wasting definition*	MUAC < 115 mm or WHZ < − 3 or bipedal oedema	MUAC (115–124 mm) or − 3 < WHZ < − 2 and without bipedeal oedema		MUAC < 125 mm or bipedal oedema			MUAC < 125 mm or bipedal oedema	
				MUAC < 115 mm or bipedal oedema	MUAC 115–119 mm	MUAC 120–124 mm	MUAC < 115 mm or bipedal oedema	MUAC 115–124 mm
*Treatment product and quantity*	RUTF 150–200 kcal/kg/day	If aged 6–23 months: super cereal plus 200 g/day (~ 787 kcal/day) or RUSF, one 92 g sachet/day (500 kcal/day)	If aged 24–59 months: no supplementation	RUTF 170–200 (kcal/kg/day)	RUTF 125–190 (kcal/kg/day)	RUTF 50–166 (kcal/kg/day)	RUTF 1000 kcal/day (2 sachets/day)	RUTF 500 kcal/day (1 sachet/day)
*Calculation of dosage*	According to the weight	Fixed amount, regardless of weight or MUAC status	–	According to MUAC status and weight			According to MUAC status	
*Frequency*	Weekly	Weekly	No visit	Weekly	Weekly	Weekly	Weekly	Weekly
*Recovery definition*	• MUAC ≥ 125 mm AND WHZ ≥ − 2 for 2 consecutive weeks • No oedema for 14 days • 4 weeks of participation in the programme • Good clinical health (no fever)			• MUAC ≥ 125 mm for 2 consecutive weeks • No oedema for 2 consecutive weeks • 4 weeks of participation in the programme • Good clinical health (no fever)			• MUAC ≥ 125 mm for 2 consecutive weeks • No oedema for 2 consecutive weeks • 4 weeks of participation in the programme • Good clinical health (no fever)	

*ComPAS* Combined protocol for Acute Malnutrition Study, *MAM* moderate acute malnutrition, *MUAC* mid-upper arm circumference, *OptiMA* Optimising acute MAlnutrition, *RUSF* ready-to-use supplementary food, *RUTF* ready-to-use therapeutic food, *SAM* severe acute malnutrition, *WHZ* weight-for-height *Z*-score

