In the control arm, children included with a MUAC < 115 mm and/or WHZ < − 3 and/or nutritional oedema are treated weekly with RUTF, according to the Niger national protocol dosage table based on the child’s weight. The Niger protocol provides a RUTF daily caloric intake of 150–200 kcal/kg/day during the entire treatment schedule until recovery in children with SAM. Children under 2 years old included with a MUAC between 115 and124 mm and WHZ > − 3 without bipedal oedema are treated weekly by one sachet of RUSF per day (500 kcal/day) during the course of treatment. However, children over 2 years old meeting the same moderate anthropometric criteria are not eligible for supplementation according to the national MAM programme.

The simplified strategies apply to AM children defined as MUAC < 125 mm or bipedal oedema (+, ++) without medical complications on admission and with a good or moderate appetite test.

In contrast to the weight-based RUTF ration in the national SAM programme, the OptiMA RUTF ration is calibrated to the child’s degree of wasting based on the combination of MUAC status and weight. Thus, more nutritional support is given to the most severely malnourished children and then gradually reduced as the child’s MUAC increased. Children with MUAC < 115 mm or oedema receive 175 kcal/kg per day of RUTF. Children with MUAC 115–119 mm, either at admission or during the course of treatment, receive 125 kcal/kg per day of RUTF, and children with MUAC ≥ 120 mm receive 75 kcal/kg per day of RUTF (with a minimum of one sachet/day) until discharge from the programme.

The ComPAS strategy is the most simplified protocol, not requiring a dosage table and proposing to gradually reduce the dosage according to the child’s MUAC status only during the outpatient follow-up as follows: 2 sachets/day of RUTF to children with MUAC < 115 mm or oedema and 1 sachet/day for children in the 115–124 mm MUAC zone.

For both simplified strategies, children with oedema receive the same RUTF ration as children with MUAC < 115 mm until oedema are resolved, at which point their ration is determined by MUAC and weight.

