**Assessments**				
Nutritional and medical assessment	x	x	x	x
Hospitalisation if required		x	x	x
Adverse event		x	x	x

^1^Minimum of 4 weeks of RUTF supplementation and a maximum of 16 weeks for the first episode of AM and if relapse

^2^After discharge from the outpatient visit or for children not eligible for supplementation (standard arm aged 24–59 months with a MUAC 115–124 mm and WHZ > − 3 and no oedema)

^3^At the discharge outpatient visit

Failure to reach recovery criteria is defined after 16 weeks in the programme, then children are discharged from OTF as non-responders and consulted once a month at home until they reach the 6-month post-inclusion. For each non-responder discharged with a MUAC < 115 mm, a medical committee meets to decide on the medical follow-up of the child in the trial. Defaulters are defined as a child absent for 3 consecutive visits. CHWs trace children who are absent to motivate caretakers to return to the health facilities. If caretaker refuse to return to the health centre, the child is followed up once a month at home until the 6-month post inclusion period. When caretakers refuse the follow-up at home, the exit status of children is declared “confirmed defaulter” when the vital status is known and “lost to follow-up” when the vital status is unknown.

Children are discharged from outpatient treatment according to the anthropometric exit criteria of their allocation arm. In standard protocol, children need to achieve a MUAC ≥ 125 mm and a WHZ ≥ − 2 without oedema for two consecutive weeks while in OptiMA and ComPAS strategies, children will be discharged if they reach a MUAC ≥ 125 mm without oedema for two consecutive weeks. For each arm, all children will have to participate a minimum of 4 weeks in the programme with good clinical health (absence of fever) to be discharged from the OTF.

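### Non-response in the overall population is not comparable across arms, because untreated control children over 2 years cannot meet the recovery criteria; relapse and RUTF per recovered child inherit this

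*Protocol article*

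**What the plan says.** All references are to the protocol article.

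- **Population.** Footnote a of Table 1: "All the secondary outcomes will be analysed for the overall population". It defines that population as MUAC < 125 mm or WHZ < −3 or oedema, and adds the two SAM populations.
- **Non-response.** Table 1: "Children who did not reach the recovery criteria", with the time point 16 weeks after inclusion. The Objectives section lists "non-response after outpatient follow-up", and the Follow-up section says "Failure to reach recovery criteria is defined after 16 weeks in the programme".
- **Relapse and RUTF per recovered child.** Table 1 counts both among children who have recovered.
- **Recovery.** The duration element is worded in three ways: "a 4-week minimum duration of RUTF treatment" (Table 1), "a 4-week minimum duration of treatment" (Study outcomes, for the two SAM subgroups) and "4 weeks of participation in the programme" (Table 2). Each version also requires the MUAC target for two consecutive weeks.
- **Control care for non-SAM children.** Those under 2 years "are treated weekly by one sachet of RUSF per day (500 kcal/day) during the course of treatment" (Intervention). Those over 2 years receive no supplement (Intervention), have no programme visit (Table 2) and go straight to monthly home visits after inclusion (Follow-up).
- **OptiMA and ComPAS.** All non-SAM children receive RUTF and are seen weekly.

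**The concern.** Recovery needs a period of treatment and two consecutive weekly readings. A non-SAM control child aged 24–59 months has neither on assigned care. Such a child may regain a MUAC of 125 mm or more and still not be classed as recovered, whereas a child with the same course in OptiMA or ComPAS would be.

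The stated time points then lead to different results. Counting from inclusion makes these controls non-responders whatever their anthropometry. Counting from programme entry or outpatient follow-up removes them from the control denominator while their counterparts stay in the other two. Neither compares like with like.

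The Statistical analysis section allows the other secondary outcomes to be tested for superiority, where appropriate, once non-inferiority is shown. A difference in non-response that comes partly from the definition could then be reported as a benefit of the simplified strategies.

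**Working it through.** **Who can be classed as recovered, on assigned care (programme wording of Table 2)**

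- SAM, any arm: weekly RUTF visits; can meet the criteria.
- Non-SAM, OptiMA or ComPAS, any age: weekly RUTF visits; can meet them.
- Non-SAM, control, 6–23 months: weekly RUSF visits; can meet them.
- Non-SAM, control, 24–59 months: no product, monthly home visits; cannot meet the duration element or show two consecutive weeks.

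**Inputs**

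- Planned size per arm is 568 (primary) and 384 (MUAC < 115 mm or oedema). These reproduce: a 10-point margin and one-sided 1.25% give 541 and 366, and × 1.05 gives 568 and 384.
- Pilot recovery under OptiMA (Sample size): 91% non-SAM, 70% SAM, 57% MUAC < 115 mm. Overall pilot recovery exceeded 80%, and 290 of 1111 children had MUAC < 115 mm (Introduction).
- Assumed, because the article does not give it: the share s of non-SAM children aged 24–59 months is 10–50%.
- Assumed: true recovery is the same in every arm.

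Counts below are shown rounded; unrounded values were carried through.

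**Non-SAM share of the first 568**

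- Lower: (80 − 70)/(91 − 70) = 0.476, or 270 children.
- Upper: the MUAC < 115 mm share is 290/1111 = 0.261. If all other SAM children recovered, the SAM share would be 0.261 × (1 − 0.57)/(1 − 0.70) = 0.374. The non-SAM share is then at most 0.626, or 355 children.

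**After the SAM-only top-up (Randomisation section)**

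- MUAC < 115 mm among the first 568: 0.261 × 568 = 148. Still needed: 384 − 148 = 236. Total 804 per arm.
- Non-SAM share q = 270/804 = 0.337 to 355/804 = 0.442.
- SAM children recovered, R = 298 × 0.70 + 236 × 0.57 = 343, or 213 × 0.70 + 236 × 0.57 = 283.
- Non-response in the simplified arms: 26.7% (q = 0.337) or 24.5% (q = 0.442).

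**Case 1: untreated controls counted as failures**

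The gap due to the definition is r × q × s, where r is the share of untreated controls who would truly recover.

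- r = 0.91: 0.91 × 0.337 × 0.1 = 3.1 points, to 0.91 × 0.442 × 0.5 = 20.1 points.
- r = 0.60 (illustrative): 0.60 × 0.337 × 0.1 = 2.0 points, to 0.60 × 0.442 × 0.5 = 13.3 points.
- If the top-up first fills SAM to 295, the upper total is 829 and q = 0.429. The upper end at r = 0.91 becomes 0.91 × 0.429 × 0.5 = 19.5 points.

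**Case 2: untreated controls left out of the control denominator**

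- Removed: 270 × 0.1 = 27, to 355 × 0.5 = 178 children (3–22% of the arm).
- Lower: control recovery (588.8 − 24.6)/(803.7 − 27.0) = 0.726, so non-response is 27.4% against 26.7%, a gap of 0.6 points.
- Upper: (606.6 − 161.7)/(803.7 − 177.7) = 0.711, so 28.9% against 24.5%, a gap of 4.4 points.

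**Effect on relapse**

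The SAM share among recovered children is R/(R + 0.91N) in the simplified arms and R/(R + 0.91N(1 − s)) in control, with N the non-SAM count.

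- N = 270: 343/(343 + 246) = 58%, against 61% (s = 0.1) to 74% (s = 0.5).
- N = 355: 283/(283 + 323) = 47%, against 49% to 64%.

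Relapse is therefore compared between groups of different severity. RUTF per recovered child omits control children who used no RUTF, which raises the control mean.

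**The case against.** - **Denominators belong in the analysis plan, and footnote a is a summary.** Two Table 1 rows are indeed confined to SAM children, so the footnote cannot be literal for every row. But the three rows at issue carry no such limit, and the definitions that are printed already give an arm-dependent result. This is more than missing detail.
- **The Objectives and Follow-up sections tie non-response to outpatient care, so untreated children are not natural non-responders.** This is a fair reading, and it gives the smaller gap of 0.6–4.4 points. It does not remove the problem, because only the control denominator shrinks.
- **Giving no supplement over age 2 is part of the national strategy, so a difference may be real.** This stands in part. Only children who would truly recover without treatment are misclassified, which is why 91% gives an upper figure.
- **Village visits count towards recovery, and children can be referred into care.** The sentence on village visits concerns the two SAM subgroups, and monthly visits cannot show two consecutive weeks. Later referral is possible, so the point is limited to assigned care.
- **These are lower-tier outcomes, and superiority is conditional.** This stands, and it limits the weight of the point.

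A reader might go further and take Table 1's RUTF wording literally. RUSF-treated controls under 2 years would then fail too, and the gap would be 0.91q, about 31–40 points. The documents do not support that. The Study outcomes section words the element without naming a product and confines it to the two SAM subgroups, and Table 2 asks only for time in the programme, which weekly RUSF children have. The wording in Table 1 is probably loose drafting.

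**Conclusion.** The point holds for non-SAM control children aged 24–59 months. As defined, non-response in the overall population is not comparable across arms, and relapse and RUTF per recovered child carry the same fault. The direction favours OptiMA and ComPAS on non-response.

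The size is not known. It is at most about 3–20 points if these controls count as failures and 91% of them would truly recover, with proportionally less for a lower rate. It is about 0.6–4.4 points if they are left out. Both ranges rest on an assumed 10–50% age share, on pilot recovery rates seen under OptiMA, and on a non-SAM share inferred from pilot figures.

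A reader might infer that the trial's main conclusions are at risk. They are not, on this point. The primary outcome has no treatment-duration element, and the two main secondary outcomes cover only SAM children, who receive RUTF in every arm. The change is worth making because the outcomes may be tested for superiority and the correction is cheap.

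**What to change.** 1. In the Recovery row of Table 1, replace the RUTF-specific duration with four weeks in the programme, as in Table 2.
2. Compare non-response, relapse and RUTF per recovered child between arms only among randomised SAM children. Exclude the children with WHZ < −3 and MUAC ≥ 125 mm, who enter control without randomisation. State that control discharge also needs WHZ ≥ −2, so treatment length and RUTF use still follow different exit rules within SAM.
3. For the overall randomised population, use one anthropometric status for all arms (MUAC ≥ 125 mm, WHZ > −3, no oedema) at the weekly or home visit nearest 16 weeks, and keep RUTF per child with a favourable outcome.

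The cost is an edit to Table 1 and its footnote. No visits or measurements are added. The small loss is that recovery-based outcomes are no longer compared in the overall population.

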### Sample size

We determined the sample size using an expecting success rate of 68% in each arm for the principal objective and a recovery rate of 82% and 74% for the main secondary objectives #1 and #2, respectively. These hypotheses were based on the results found in the pilot non-comparative cohort study implemented in the Mirriah district in 2019 (Personal communication, 2020). Recovery rates under OptiMA protocol were estimated at 91%, 70%, and 57% for children admitted with a MUAC between 115 and 124 mm and WHZ > − 3, those with SAM according to the WHO definition, and those with MUAC < 115 mm, respectively. In the OptiMA-Niger trial, recovery is defined throughout the 6-month follow-up which will increase these estimations. After having been discharged from this study, non-responders and a sample of recovered children were also seen 6 months after their exit in order to estimate a relapse rate. We estimated that children will be followed up on average 4 months after discharge with a relapse rate of 30%.

To demonstrate non-inferiority of the OptiMA or ComPAS strategies with standard protocol, we assumed a non-inferiority margin of 10%, the same as in other non-inferiority trials assessing simplified protocol [11, 13]. We reduced the test significant level (alpha) at 1.25 to consider the multiple testing [17], a power of 90% for the main objective and 80% for the 2 main secondary objectives were applied, and an inflation rate of 5% was used to account for unexploitable data. Calculations were performed using the SAS software (Proc Power TwoSampleFreq). For the principal objective, 568 children are required per arm, and 295 and 384 children per arm for the main secondary objectives #1 and #2, respectively.

### Randomisation

Randomisation was performed using specially developed software, containing lists prepared in advance by an independent statistician, and inaccessible to trial staff. The randomisation is done in blocks (block size is kept confidential) and stratified at the study site by the severity of AM according to the following criteria: MUAC < 115 mm or oedema, MUAC > 115 mm and WHZ < − 3, and MUAC between 115 and 124 and WHZ > − 3 without oedema. This stratification allows for the recruitment of comparable groups of SAM WHO, MUAC < 115 mm, and non-SAM children and for simultaneous randomisation at the four sites. Once the randomisation was decided by the investigator on the basis of the verification of the eligibility criteria, they interrogated this software, which assigned the code and the corresponding treatment. This software assigns a treatment arm by sequentially drawing from this list each time a randomisation procedure is completed. After the children were assigned to an arm by the software, the trial and clinic staff were informed of the assigned treatment and therefore became unblinded. Once the sample size for the primary objective will be reached, only SAM WHO and then MUAC < 115 mm or oedema children will continue to be enrolled and randomised until the sample size required for the two main secondary objectives will be attained.

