The Optimsing treatment for Acute Malnutrition (OptiMA) strategy has been developed in a research consortium between humanitarians from the Alliance for International Medical Action (ALIMA) non-governmental organisation and scientists from the French National Institute for Health and Medical Research (Inserm). The OptiMA RUTF ration is calibrated to the child’s degree of wasting based on the combination of MUAC status and weight. Thus, more nutritional feeding is given to the most severely malnourished and then gradually reduced as the child’s MUAC increased. Children with MUAC < 115 mm or oedema receive 175 kcal/kg/day of RUTF. Children with MUAC 115–119 mm, either at admission or during the course of treatment, receive 125 kcal/kg/day of RUTF, and children with MUAC ≥ 120 mm receive 75 kcal/kg/day of RUTF (with a minimum of one sachet/day) until discharge from the programme. The OptiMA strategy was first implemented in a proof-of-concept single-arm trial in Burkina Faso in 2018 [10]. The results showed a recovery rate that exceeded SPHERE standards among children admitted with MUAC < 125mm (86.3%; 95% CI 85.4–87.2%) with an excellent health worker adherence to the new RUTF table. However, recovery among children admitted with a MUAC < 115 mm or oedema was poorer than anticipated (70.4%; 95% CI 67.5–73.5%). Then, an individually randomised non-inferiority controlled trial compared the OptiMA strategy to the national protocol was implemented in the Democratic Republic of the Congo (DRC) in 2019 [11]. The OptiMA protocol treated 29% more children with 20% less nutritional inputs compared to the standard protocol. A pilot non-comparative cohort study on 1111 acutely malnourished children per the OptiMA definition was implemented in 2019 in Niger and showed a similar result to the one observed in the above-mentioned study in Burkina Faso with a global recovery rate among children admitted with a MUAC < 125 mm that exceeded 80% ( [10] and Personal communication, 2020). However, recovery among the 290 children admitted with a MUAC < 115 mm remained low (57.7%), partly explained by a high proportion of children (34.1%) not reaching the exit criteria after 10 weeks of participation in the programme (Personal communication, 2020).

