### Children selection procedure and enrolment

Prior to enrolment, the research team composed of community health workers (CHWs), nurses, clinical trial technicians, clinical trial monitors, data mangers, and Ministry of Health (MoH) medical staff implicated in the study were trained on the trial protocol, standardised operating procedures (SOP), and the correct use of IT tools developed for data collection. Clinical trial technicians were specifically trained to enrol and randomise study participants and to monitor home visits and outpatient visits at the health centre. Due to the SARS-Cov-2 pandemic, all staff were also trained on barrier measures (wearing a mask, physical distancing, interviewing outside, washing hands).

Children are directly recruited when they presented for outpatient consultation in one of the four health centres selected in the trial. To ensure the data quality required in a randomised controlled trial and to cover the AM peak (July to October), we control the number of inclusions per day. A maximum threshold is fixed at 7 inclusions per day and per clinical trial technician. When more than 7 children are eligible per day in a health centre, a standard operating procedure to ensure a random selection of children is implemented. Mothers with their children are used to arriving early at the health centre. MoH staff in charge of the screening at admission give a numbered card to the mother if the child is eligible for the trial (anthropometric criteria, age, and place of residence). Once most of the mothers have arrived, the research field coordinator is informed by phone of the number of eligible children and proceeds to the randomised selection of children from numbered balls in a bag. The following data on age, sex, MUAC, WHZ, and distance between the village and the health centre are collected for all eligible children to check on the representativeness of the sample. Children randomly selected are proposed to participate to the trial, and the others do not participate in the trial and follow the standard protocol.

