### Statistical analysis

All statistical analyses will be performed using the RStudio Software (Boston, MA, USA) as specified by the data analysis plan published on ClinicalTrials.gov prior to performing any analysis. Statistical tests will be carried out bilaterally with an alpha risk of 5% and unilaterally with an alpha risk of 1.25% for the non-inferiority analysis. Qualitative variables will be described in terms of numbers and percentages and provided with CIs when relevant. If necessary, comparisons of qualitative variables will be made using *χ*^2^ or Fisher exact tests. Quantitative variables will be described in terms of mean, SD, and CI or median, range, and IQR. If necessary, comparisons of quantitative variables will be made using Student’s, Wilcoxon’s, or Kruskal-Wallis tests, depending on the distribution of the variable of interest. Time delay type variables will be described in terms of the incidence of occurrence, and the probability of occurrence over time, estimated by the Kaplan-Meier method. If necessary, probability comparisons will be made using log-rank tests, or proportional risk models, after verification of the assumption of proportionality of risks.

The main analysis of the primary and secondary outcomes will be intention-to-treat and per-protocol given that this is a non-inferiority trial. Participants included in the main analyses will be described according to the diagram defined by CONSORT (Consolidated Standards of Reporting Trials) recommendations [18]. The occurrence of the primary “favourable outcome” and the secondary main outcome “recovery” will be compared between the two randomisation arms. These two comparisons will be performed both by “intention-to-treat” basis and on a “per-protocol” basis. Non-inferiority analyses will be performed on these two outcomes. Only if non-inferiority for these two outcomes is demonstrated will the other secondary analyses will be performed and, if appropriate, as a superiority analysis. Superiority will be particularly sought for cost outcomes related to RUTF cost-efficiency.

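### No cut-off is stated between the primary analysis set and the later severity-restricted recruitment, so read literally the primary result would describe a more severe mix than the caseload

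*Protocol article*

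**What the plan says.** The Sample size section of the protocol article gives three targets: "568 children are required per arm, and 295 and 384 children per arm for the main secondary objectives #1 and #2, respectively". The first rests on "an expecting success rate of 68% in each arm for the principal objective", the other two on "a recovery rate of 82% and 74% for the main secondary objectives #1 and #2, respectively". These rates are attributed to a pilot cohort in the same district.

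The Randomisation section stratifies allocation by three severity levels. It then says of recruitment after the primary target is met: "only SAM WHO and then MUAC < 115 mm or oedema children will continue to be enrolled and randomised until the sample size required". The size meant is that of main secondary objectives #1 and #2.

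On the analysis set, the Statistical analysis section says: "The main analysis of the primary and secondary outcomes will be intention-to-treat and per-protocol". It gives no enrolment cut-off for the primary outcome and no stratification or weighting by severity, and it refers to a separate data analysis plan, which is not at hand. The footnote to Table 1 defines the overall population for the secondary outcomes by anthropometry alone, also without a cut-off.

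The Introduction and Objectives frame the primary question as the treatment of uncomplicated SAM and MAM together.

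**The concern.** Intention-to-treat ordinarily means every randomised child. Combined with the recruitment rule, that puts a stage of SAM children only, and then of MUAC < 115 mm or oedema children only, into the primary comparison. The population described by the primary risk difference would then be set partly by the sample size of a secondary objective, not by the district's caseload, on which the 68% rate and the hypothesis rest.

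This matters because effects may well differ by severity. In the control arm, SAM children keep a weight-based ration until recovery, whereas both strategies taper. Control MAM children aged 24–59 months receive no supplementation, whereas both strategies give RUTF. If the true difference varies across strata, its pooled value depends on the mix.

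Objective #1 (SAM by the WHO definition) has the same problem on a smaller scale, because the last stage adds only its MUAC < 115 mm part.

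**Working it through.** **Step 1: reproduce the plan's sample sizes.** Inputs from the Sample size and Statistical analysis sections: equal rates in both arms, "we assumed a non-inferiority margin of 10" percentage points, one-sided alpha 1.25%, power 90% or 80%, 5% inflation.

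n per arm = (z₁₋α + z_power)² × 2p(1−p) / 0.10²

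- Primary: (2.2414 + 1.2816)² × 2 × 0.68 × 0.32 / 0.01 = 540.1; × 1.05 = 567.1, so 568.
- #1: (2.2414 + 0.8416)² × 2 × 0.82 × 0.18 / 0.01 = 280.6; × 1.05 = 294.6, so 295.
- #2: (2.2414 + 0.8416)² × 2 × 0.74 × 0.26 / 0.01 = 365.8; × 1.05 = 384.0, so 384.

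All three stated figures are reproduced.

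**Step 2: will there be an extension?** MUAC < 115 mm or oedema children are a subset of SAM, so the target of 384 drives recruitment past the 295. No extension is needed only if 384/568 = 67.6% of the first 568 per arm are in that group. The Introduction reports "recovery among the 290 children admitted with a MUAC" below 115 mm out of 1,111 in the pilot, a share of 290/1,111 = 26.1%.

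**Step 3: the resulting mix.** Assumptions: the pilot share holds, and 10% of randomised children have WHZ < −3 with MUAC 115–124 mm (the documents give no figure; range 5–20% below). The SAM-only stage runs until 295 SAM children per arm.

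- First 568 per arm: MUAC < 115 mm 148.2, WHZ-only SAM 56.8, non-SAM 363.0.
- SAM-only stage: 295 − 205.0 = 90.0 more, split 26.1 to 10, giving 213.3 and 81.7.
- MUAC < 115 mm stage: 384 − 213.3 = 170.7 more.
- Total: 384 + 81.7 + 363.0 = 828.7 per arm. MUAC < 115 mm share: 384/828.7 = 46.3%.
- Within SAM (objective #1): 148.2/205.0 = 72% before, 384/465.7 = 82% after.

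| Natural MUAC < 115 mm share | WHZ-only SAM (assumed) | Total per arm | Share if all pooled |
|---|---|---|---|
| 20% | 10% | 880 | 44% |
| 26.1% | 5% | 823 | 47% |
| 26.1% | 10% | 829 | 46% |
| 26.1% | 20% | 818 | 47% |
| 30% | 10% | 799 | 48% |
| 40% | 10% | 727 | 53% |

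**Step 4: what the mix can do to the verdict.** Illustrative assumptions, not in the documents: control favourable rates of 55% (MUAC < 115 mm) and 70% (others). With pooled difference d, P(non-inferiority) = Φ[(d + 0.10)/SE − 2.2414]. Evaluable n per arm is 541 with a cut (the uninflated size) and 829 × 0.95 = 788 if pooled.

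| True effect: MUAC < 115 mm / others | d, cut (26.1%) | P, cut | d, pooled (46.3%) | P, pooled |
|---|---|---|---|---|
| 0 / 0 | 0 | 89% | 0 | 97% |
| −12 / 0 points | −3.1 | 55% | −5.6 | 33% |
| +5 / −10 points | −6.1 | 18% | −3.1 | 72% |

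For example, in the second row with a cut: d = 0.261 × (−0.12) = −0.0313, SE = 0.0291, and 0.0687/0.0291 − 2.2414 = 0.12, so Φ = 0.55. A simpler calculation that ignores WHZ-only SAM (48% share, 764 evaluable per arm) gives 30% instead of 33%.

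**Step 5: precision from stratifying.** Gain = 1 − within-stratum variance / total variance. At the assumed 55%/70% it is 1.9% with a 26.1% share and 2.4% with 46.3%.

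**The case against.** The strongest reply is that the article is silent: it does not say that the extension is pooled. Analysis-set definitions are commonly left to the analysis plan it cites. The extension is also said to start once the primary sample size is reached and to serve the secondary objectives, which can be read as closing the primary set. The silence is real, so a reader who infers that the plan prescribes an uncut, unstratified primary analysis goes further than the text. What remains is that the recruitment sentence governs enrolment and does not define an analysis set, while the analysis sentence, taken in its ordinary meaning, includes everyone randomised.

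Other tempting readings also fail:

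- **Unstratified test.** The chi-squared and Fisher sentence is generic. No method is named for the non-inferiority comparison.
- **Bias between arms.** Randomisation is stratified by severity and later children go to all three arms, so the comparison stays fair. The issue is which population it describes.
- **Pooling favours a false non-inferiority claim.** With −12/0 it makes the claim harder; with +5/−10 it makes it easier. Under equal rates, power rises.
- **Strategies give less to all SAM and more to all MAM.** Table 2 does not support this. OptiMA's range below 115 mm (170–200 kcal/kg/day) is not lower than control's 150–200. ComPAS at 115–124 mm and control RUSF under 2 years both give 500 kcal/day.
- **Arbitrary length.** The extension stops at a prespecified 384 per arm.

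A large difference below 115 mm would also be tested directly in objective #2, and the Discussion ties its advice on dose reduction to each objective. That limits the practical harm but does not define the primary population.

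**Conclusion.** The concern holds as one of estimand and generalisability. Two stated rules, each sensible alone, combine under their ordinary reading into a primary population that is not the uncomplicated acute malnutrition caseload. On the pilot share, with 5–20% WHZ-only SAM assumed, MUAC < 115 mm children go from 26% to about 46–47% of the primary set, at about 820–830 per arm. For natural shares of 20–40% the result is about 44–53%. Objective #1 tilts from about 72% to 82% MUAC < 115 mm in the central case.

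The shift in the mix rests on the pilot share, which counts MUAC < 115 mm and may not include all oedema cases. The effect on the verdict rests on assumed effects that differ by severity; if effects are equal across strata, pooling costs nothing. The cited analysis plan may already settle the matter.

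**What to change.** 1. State that the primary intention-to-treat and per-protocol sets comprise children randomised before recruitment was first restricted by severity, and that later children contribute only to the main secondary objectives. Alternatively, keep all children and standardise the risk difference to the pre-restriction severity mix.
2. For objective #1, use children randomised before the restriction to MUAC < 115 mm or oedema, or weight to the natural SAM mix. The screening data that "are collected for all eligible children to check on the representativeness of the sample" (Children selection procedure and enrolment) were planned for checking the daily random selection, but they include MUAC and WHZ and could supply the weights.
3. Estimate the non-inferiority risk differences stratified by the randomisation severity strata (for example Mantel-Haenszel), with limits matching the one-sided 1.25% level, and show each stratum's difference.

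Cost: wording only, since randomisation dates and severity are already recorded. With a cut-off, the roughly 260 extension children per arm (829 − 568, central case) add nothing to the primary analysis, which keeps its planned 568 per arm and about 90% power. The precision gain from stratifying is small, about 2% of variance at the assumed rates; its main value is to show whether the effect varies with severity.
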